## Abstract

**Background:**

Approximately 30% of children with idiopathic nephrotic syndrome develop a complicated course with frequent relapses or steroid dependency. Rituximab, a B cell depleting monoclonal antibody, is a safe and effective alternative to steroids or other immunosuppressants for achieving and maintaining remission in this population at short term. Despite the good initial response relapses inevitably occur after regeneration of B lymphocytes, necessitating either repeat courses of rituximab or addition of another steroid-sparing immunosuppressant.

**Methods:**

This is a prospective, single-center, open-label, two-parallel-arm randomized controlled phase III study among children with steroid dependent nephrotic syndrome who are maintained in remission with oral steroids. One hundred children will be randomized to either Rituximab and maintenance Mycophenolate mofetil (A) or repeated courses of prophylactic Rituximab only (B). In arm A, mycophenolate mofetil (1200 mg/m^2^ per day) will be started 3 months after Rituximab administration. In arm B, Rituximab infusions will be administered at 0, 8 and 16 months if B cell count normalize at the given time points. Prednisolone will be discontinued in both groups 2 weeks following first course of rituximab. Primary aim is to evaluate the difference in 24-month relapse-free survival. Main secondary endpoints are cumulative prednisolone dose, frequency of relapses and changes in anthropometry. Circulating B lymphocyte populations will be studied as biomarkers or predictors of rituximab responsiveness and adverse events will be analysed.

**Discussion:**

The study will provide evidence as to the comparative safety and efficacy of two alternative steroid-sparing therapeutic options in children suffering from steroid dependent nephrotic syndrome. The two-year study design will address the long-term results obtained with the alternative treatment protocols.

**Trial registration:**

This trial was prospectively registered to the Clinicaltrial.gov (NCT03899103 dated 02/04/2019; https://clinicaltrials.gov/) and Clinical Trials Registry of India (CTRI/2019/04/018517 dated 09/04/2019).

## Background

Whilst idiopathic nephrotic syndrome in children usually responds well to corticosteroid treatment, more than two thirds of patients experience relapses and 30% develop a complicated course with frequent relapses or steroid dependency (SDNS) [1–7]. Relapses may lead to serious complications from anasarca, infections, thrombosis and malnutrition. Repeated or even continuous steroid treatment leads to considerable medication related toxicity and morbidity [1–6].

Hence, the primary aim of treatment is to reduce the number of relapses, the cumulative dose of corticosteroids, and the incidence of serious complications. Several prospective studies have suggested that Rituximab, a B-lymphocyte depleting monoclonal antibody, could be a safe and effective alternative to steroids and conventional steroid-sparing immunosuppressants such as calcineurin inhibitors or mycophenolate-mofetil (MMF) to achieve and maintain remission in this population [7–11]. Single rituximab infusions reliably suppress disease relapses for 6 to 12 months with a very mild side effect profile [7–11]. In the RITURNS trial we demonstrated a significant and clinically relevant reduction of relapse rates by primary use of Rituximab as compared to standard CNI therapy during a 12-month observation period, accompanied by a more favourable side effect profile [7]. However, relapses inevitably occur during extended follow-up following regeneration of B-lymphocytes. Therefore, further modification of Rituximab treatment, including repeated courses of Rituximab or adjunct immunosuppressive therapies, may be necessary for maintaining long-term remission. A few case series suggested that maintenance therapy with MMF after rituximab administration was effective for maintaining long-term remission in children with complicated nephrotic syndrome, with a largely benign side effect profile [12–14]. The long term follow up of our RITURNS trial also revealed improved relapse free survival with maintenance MMF therapy following rituximab re-exposure [14]. Hence, repeated courses of Rituximab or sequential maintenance therapy with MMF following the initial Rituximab course have been proposed as long-term treatment options in SDNS [7–11]. Our study will compare the relative efficacy and safety of these protocols over a 2-year period.

## Methods/design

### Aim, design and setting of the study

The RITURNS II trial is a prospective, single-center, open-label, two-parallel-arm randomized controlled phase III study. The aim is to evaluate the efficacy and safety of repeat courses of Rituximab to that of maintenance MMF following a single course of Rituximab in maintaining remission over 24 months in children with SDNS (as defined in Table 1). The test hypothesis is as follows: prophylactic repeated courses of Rituximab will result in improved relapse free survival compared to maintenance Mycophenolate Mofetil following single course of Rituximab infusion in children with steroid dependent nephrotic syndrome (SDNS), i.e., testing superiority.

**Table 1 Tab1:** Standard definitions for nephrotic syndrome used in this document

*Remission*	Urine albumin nil or trace (or proteinuria < 4 mg/m^2^/h or uPCR < 200 mg/g (< 20 mg/mmol)) for 3 consecutive early morning specimens
*Relapse*	Urine albumin 3+ or 4+ (or proteinuria > 40 mg/m^2^/h or uPCR ≥2000 mg/g (≥200 mg/mmol)) for 3 consecutive early morning specimens, having been in remission previously
*Steroid dependence*	Two consecutive relapses when on alternate day steroids or within 14 days of its discontinuation

*uPCR* Urine protein creatinine ratio

The trial was started on 15th May, 2019 at the Division of Pediatric Nephrology, Department of Pediatrics, NRS Medical College & Hospital, Kolkata, India. By 15th September 2020, 70 patients have been enrolled in the trial.

### Characteristics of participants

Inclusion criteria: children between 3 and 16 years with SDNS; minimal change disease/FSGS/MesPGN as per kidney biopsy report; estimated glomerular filtration rate (eGFR) > 80 ml/min per 1.73 m^2^ at study entry; remission at study entry (urine albumin nil or trace (or proteinuria < 4 mg/m^2^/h or uPCR < 200 mg/g (< 20 mg/mmol)) for 3 consecutive early morning specimens); not received any steroid sparing agent (including levamisole, calcineurin inhibitors, mycophenolate mofetil, cyclophosphamide, mizoribine, chlorambucil or rituximab) previously; parents willing to give informed written and audiovisual consent; and ability to swallow tablet.

Exclusion criteria: known etiology (e.g., lupus erythematosus, IgA nephropathy, amyloidosis, malignancy, other secondary forms of NS); patients with severe leukopenia (leukocytes < 3.0× 1000 cells/mm^3^), severe anemia (haemoglobin < 8.9 g/dl), thrombocytopenia (platelet < 100.0 × 1000 cells/mm^3^) or deranged liver function tests (AST or ALT to > 50 IU/L) at enrolment; known active chronic infection (tuberculosis, HIV, hepatitis B or C); and live vaccination within 1 month prior to screening.

### Processes, interventions and comparisons

#### Participant screening and recruitment

Consecutive cases of SDNS presenting at the study centre will be screened for eligibility. A preliminary interview for clinical and pharmacological history will be performed in order to verify the eligibility criteria. All participants undergo kidney biopsies before enrolment in the trial. A study investigator will explain the project, deliver information sheet. Children fulfilling the inclusion criteria will be recruited. The Pediatric Nephrology Division of NRS Medical College & Hospital, Kolkata is one of the largest dedicated pediatric nephrology services at Government Sector in India. An average of 140–180 children are seen per week in the nephrotic syndrome outpatient clinic; approx. 20–30% of these are new cases and about 60–80% of new cases are SDNS.

#### Interventions

##### Arm a (rituximab and mycophenolate mofetil, control treatment)

First Course Rituximab at Randomization: Two infusions will be administered intravenously at a 7-day interval at standard dose (rituximab 375 mg/m^2^, maximum 500 mg). Circulating B cells will be measured 24 h after second rituximab administration. If B cell count exceeds 5/mm^3^, it will be measured again after 1 week. If count is still > 5/mm^3^, one more dose of rituximab will be administered.

Co-intervention with Rituximab at Randomization: Prednisolone will be continued at alternate-day doses for 2 weeks (1.5 mg/kg (max.40 mg) per 48 h in patients on daily prednisolone at time of randomization; pre-randomization dose in those already on alternate-day dosing). At 2 weeks, prednisolone will be discontinued.

Addition of Maintenance MMF from month 4 onwards: Maintenance oral MMF 1200 mg/mt^2^ daily in two divided doses will be added from month 4 of follow-up and continued over the remaining study period unless an adverse event occurs.

##### Arm B (repeated courses of rituximab only, experimental treatment)

First Course Rituximab at Randomization: Same as Arm A.

Co-intervention with Rituximab at Randomization: Same as Arm A.

Prophylactic 2nd and 3rd Course Rituximab Re-administration at 8 Months and 16 Months of Follow-up: Prophylactic 2nd and 3rd course rituximab re-administration will be done at 8 months and 16 months of follow-up if B cell count normalize (please refer to Additional file 1: Appendix 0 for our reference range of normal age specific B cell count) and patient is in remission. Dose and route will remain as explained in Table 2.

**Table 2 Tab2:** Intervention in both arms over time

	Group A (RITUX +MMF)	Group B (Repeated RITUX only)
At randomization	First course rituximab. Stop steroid at 14 days.	First course rituximab. Stop steroid at 14 days.
At month 4	Add MMF and continue over study period unless any adverse event	–
At month 8	–	2nd course prophylactic rituximab if B cell normalize.
At month 16	–	3rd course prophylactic rituximab if B cell normalize.
At month 24	FOLLOW-UP COMPLETED	
	Any relapse during the observation period will be treated with prednisone (2 mg/kg/day) until remission, followed by 1.5 mg/kg alternate day for 1 month.	
If > = 2 relapses during any 6 month period, treat by	2nd course rituximab if B cell in normal range. Continue MMF.	Add MMF.

#### Comparisons, randomization & blinding

Treatment arm A will be compared to treatment arm B. Randomization will be performed 1:1 using stratified block randomization with varying block sizes and including age (≤ 7 vs. > 7 years) and renal histology (MCD vs. FSGS) as stratification factors. To achieve comparable intervention groups and to minimize a potential selection bias, patients will be allocated in a concealed fashion by means of randomization after enrolment. To that end, a computer generated random list will be created according to the stratification factors and block sizes and sealed opaque envelopes will be provided by an independent data manager from the Institute of Medical Biometry and Informatics, University of Heidelberg. Enrolment and assignment of the participants to interventions will be done by investigators and resident doctors at NRS Medical College & Hospital, Kolkata, India. The trial will be open-label with no masking of patients or study staff to the treatment allocation.

#### Study visits & assessment

##### Baseline assessment at enrolment

Retrospective clinical information will be obtained from the case records and clinic files. This will include information regarding age of onset of disease, disease type, duration of total disease etc.; and treatment received, number of relapses, cumulative steroid dose, detailed anthropometry and investigations during the last 12 months prior screening. The patients shall be clinically screened for significant infection. The information will be entered into the patient data sheet (refer to Additional file 1: Appendix 1). Clinical examination shall be done and data shall be recorded.

##### Follow-up visit and drug compliance

Study visits will be scheduled at enrolment, then weekly for the first month, then at 4th month and then 4 monthly until the end of the study or during relapse, remission and if there is any specific need after enrolment. In Arm B (repeated courses of rituximab only), there will be 2 extra visits 1 week after the prophylactic 2nd and 3rd courses of rituximab re-administration at 8 months and 16 months, respectively.

Complete blood count, kidney function, liver enzymes, serum electrolytes, plasma proteins, serum cholesterol, serum albumin, serum immunoglobulin and B lymphocyte count as applicable will be obtained during protocol visits and in between period if needed. Circulating B-cell count (number/mm^3^) will be measured at enrolment, then every fortnight for the first month, then at 4 months and then 4-monthly until the end of the study or during relapse and if there is any specific need after enrolment. An overview is given in Table 3. At the 12- and 24-month visits a quality of life (QoL) assessment together with a specific questionnaire concerning the impact of the different treatment patterns on patient and family life shall be performed.

**Table 3 Tab3:** Participants time line and follow up data sheet over study period

	−7 days	0 days	7 days	14 days	21 days	1 month	4 months	8 months	8 months 1 wk	12 months	16 months	16 months 1 wk	24 months	Close out
BMI for age Z score	Enrolment	Allocation & intervention	–	–	–	–			–					
Height for age Z score			–	–	–	–			–					
If on Oral Steroid, Dose (Mg/kg alternate day)														
Cumulative prednisolone dose during study period (mg/kg)			–	–	–	–	–	–	–					
If on MMF, dose (mg/kg)														
Number of Rituximab injection received														
Total B Lymphocyte count:														
Any Relapse during this period														
Time to first relapse (weeks)														
Albumin (g/dl)			–		–									
Urine protein-creatinine ratio			–		–									
Blood leucoocyte count (n/mm^3^)			–		–	–								
Blood leucocyte differential count (n/mm^3^)			–		–	–								
Blood Platelet count (n/mm^3^)			–		–	–								
Haemoglobin (g/dl)			–		–	–								
Serum Sodium (meq/l)			–		–	–	–		–					
Serum Potasium (meq/l)			–		–	–	–		–					
Serum Calcium (mg/dl)			–		–	–	–		–					
Aspartate transaminase (IU)			–		–	–	–		–					
Alanine transaminase (IU)			–		–	–	–		–					
Alkaline phosphatase (IU)			–		–	–	–		–					
Fasting blood glucose (mg/dl)			–		–	–	–		–					
Immunoglobulin exam														
Cholesterol (mg/dl)			–		–									
Estimated GFR, ml/min/1.73 m^2^			–		–									
Use of any other drugs														
Clinical exam (if specific abnormal –describe below) (Hypertension-Y/N)														
Any adverse report yes/no (if yes –describe in full detail)														
Study discontinuation or withdrawal (If Yes weeks of discontinuation & reason for discontinuation) Treatment related (yes/no)														

REMARKS:

ADVERSE EVENT

At each visit, the drug will be handed over to the parent/guardian in an amount sufficient to last the interim duration; ten extra doses would be provided to ensure compliance even if follow-up is delayed for some reason. At the follow-up visit, empty packs of drug provided in previous visit would be collected and pill count done to check compliance to intervention. At discharge from the Nephrology Unit, each patient will receive a clinical diary, to be filled with dipstick proteinuria levels and current treatment. Adherence will also be recorded in the patients’ diary.

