#### Statistical analysis

The analysis will be performed on the full analysis set (FAS; according to the intention to treat principle), the per-protocol set and the safety analysis set (for details refer to Additional file 1: Appendix 3).

All documented variables will be analyzed descriptively by tabulation of empirical distribution measures accordingly to the scale level and under specification of the number of non-missing values.

The confirmatory primary analysis will be based on the FAS. The primary endpoint will be compared between the two treatment groups using a two-tailed logrank test stratified by age (≤ 7 vs. > 7 years) and renal histology (MCD vs. FSGS) at an overall type I error rate of 0.05. The survival curves will be estimated using the Kaplan-Meier product-limit method, and the corresponding confidence intervals will be calculated using Greenwood’s formula [25]. Missing values on the covariates will be imputed by a multivariate imputation model. To assess the impact of major protocol deviations, an analogous analysis of the primary endpoint will be performed on the per protocol set. In addition, the possible influence of age (continuous) and renal histology on the primary endpoint is evaluated within a multivariate Cox regression analysis including treatment group (under the assumption of proportional hazards) performed on the FAS. Furthermore, a multivariate Cox regression analysis with covariates, age (continuous), sex, renal histology (MCD vs. FSGS), duration of the nephrotic syndrome (years), number of relapses in previous year and group will be performed on the FAS. All secondary endpoints will be analyzed based on the FAS and the results will be interpreted descriptively.

The **s**afety analysis will be based on the safety analysis set and includes calculation and comparison of frequencies and rates of adverse and serious adverse events reported in the two treatment groups. Furthermore, the relation of AEs with the cumulative dose of Rituximab, MMF and Prednisolone will be described, respectively.

More details can be found in the statistical analysis plan which will be finalized prior to database closure and before performing any analyses. All analyses will employ SAS Version 9.4 or higher.

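### After month 4, mild adverse events and transient laboratory abnormalities are somewhat more likely to be recorded in arm B, because only arm B has visits one week after repeat rituximab

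*Protocol article*

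**What the plan says.** The section on follow-up visits and drug compliance sets a common schedule: visits at enrolment, "then weekly for the first month, then at 4th month and then 4 monthly until the end of the study". After month 4 this gives months 8, 12, 16, 20 and 24. Both arms may also be seen "or during relapse, remission and if there is any specific need after enrolment". For arm B only, "there will be 2 extra visits 1 week after the prophylactic 2nd and 3rd courses of rituximab re-administration at 8 months and 16 months".

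Table 3 gives these two visits their own columns. As extracted, the adverse-report row and the leucocyte, platelet and haemoglobin rows are open in both. Liver enzymes and electrolytes are open at 16 months plus one week.

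In arm A, MMF "will be added from month 4 of follow-up and continued over the remaining study period unless an adverse event occurs"; Table 2 agrees. The abstract instead puts the start three months after rituximab.

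Between visits, "each patient will receive a clinical diary, to be filled with dipstick proteinuria levels and current treatment"; adherence is recorded there too. Adverse events are not mentioned as diary content.

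The statistical analysis section plans a "comparison of frequencies and rates of adverse and serious adverse events reported in the two treatment groups". Number and severity of adverse events is secondary endpoint 9, and abnormal biochemistry or haematology (yes/no) is secondary endpoint 14. The trial is open-label.

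**The concern.** The treatments are the same in both arms until month 4, so the safety contrast of interest arises after that. From then on, a child re-treated in arm B is asked about adverse events, and has blood counts, one week after the course. A child starting MMF at month 4 is next asked on schedule at month 8. With the same true rate of minor harm in both arms, more of it would be recorded in arm B. Endpoint 14 has the same weakness without any recall: a yes/no abnormality becomes more likely the more often blood is tested.

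Comparative safety is half of the trial's aim. The discussion names missing long-term rituximab safety data as clinicians' main concern and says the trial will supply valid safety information. An ascertainment difference against the repeated-rituximab arm bears on that statement.

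**Working it through.** **Visit count.** The plan's figure of two extra visits is confirmed by the two one-week columns in Table 3. By the text, scheduled visits after month 4 are 5 in arm A and at most 5 + 2 = 7 in arm B (7/5 = 1.40). Table 3 has no month-20 column; on that count they are 4 and 6 (1.50). The text schedule is used below.

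**Time to the first scheduled query.** MMF from month 4 to month 8: 4 × 30.44/7 = 17.4 weeks. Repeat rituximab: 1 week. If MMF starts at three months, as in the abstract, the month-4 visit follows after about one month.

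**Expected extra visits.** They occur only in re-treated children, and re-treatment needs normalised B cells and remission. The discussion gives B-cell recovery after a single course as 12% at 6, 39% at 9 and 93% at 12 months.
- Linear interpolation to month 8: p = 12 + (39 − 12) × 2/3 = 30%.
- Assumptions: a child re-treated at month 8 again has probability p at month 16; a child not re-treated has recovered by month 16 with probability q, from 93% to 100%. The remission condition is ignored.
- Expected extra visits = p + p² + (1 − p)q. With p = 0.30 and q = 1: 0.30 + 0.09 + 0.70 = 1.09.
- Low end (p = 0.12, q = 0.93): 0.12 + 0.01 + 0.82 = 0.95. High end (p = 0.39, q = 1): 0.39 + 0.15 + 0.61 = 1.15.

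**Offset from relapse visits.** The sample-size section assumes 24-month event rates of 25% in arm A and 5% in arm B. With two visits per first relapse (assumption), arm A gains 2 × (0.25 − 0.05) = 0.40 visits per child. Arm B's net excess is 0.95 − 0.40 = 0.55 to 1.15 − 0.40 = 0.75, or 2 − 0.40 = 1.60 if both extra visits are held. The direction does not change.

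**Recording ratio.** Assume equal true rates, events spread evenly over months 4 to 24, and an event recorded only if a scheduled visit follows within a recall window of R months. Relapse visits are left out. Arm A covers 5R months. Each extra visit comes one week (0.23 months) after a common visit, so it adds only 0.23 months; the rest of its window is already covered. At R = 4 the common visits cover the whole period.

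| R (months) | Arm A covered | Arm B covered, 1.09 extra visits | B/A | Arm B covered, 2 extra visits | B/A |
|---|---|---|---|---|---|
| 0.25 | 1.25 | 1.25 + 0.25 = 1.50 | 1.20 | 1.25 + 0.46 = 1.71 | 1.37 |
| 1 | 5.00 | 5.25 | 1.05 | 5.46 | 1.09 |
| 2 | 10.00 | 10.25 | 1.03 | 10.46 | 1.05 |
| 4 | 20.00 | 20.00 | 1.00 | 20.00 | 1.00 |

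In weeks, months 4 to 24 are 20 × 4.35 = 87 weeks. With 4 weeks' recall, arm A covers 20/87 = 23.0% and arm B 21.09/87 = 24.2% (ratio 1.05). With 8 weeks' recall the ratio is 41.09/40 = 1.03. These ratios do not depend on which MMF start date applies; only the 17-week gap does. Events that cluster soon after drug start would widen the difference. The documents give no figures with which to size that.

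**The case against.** **What a reader might infer, and why the documents do not support it.** With 4 weeks' recall about 77% of mild events in arm A fall outside the windows, which could be read as the size of the bias. Arm B shares almost the whole gap, and the between-arm difference is just over 1 percentage point. Likewise, 1.09/(5 + 1.09) = 18% of arm B's scheduled enquiries have no counterpart in arm A. That is a share of visits, not of events captured.

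Observation of rituximab at the infusion might also be counted as bias. Infusion reactions are real harms that the safety-data section requires to be recorded, and months 8 and 16 are visits in both arms. Only the visits one week later are unequal.

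**What else stands against the point.** Relapse and remission visits, expected more often in arm A, remove over a third of the expected visit excess (0.40/1.09). The long gap after MMF start rests on one of two conflicting statements in the article. The adverse-event policy is in Additional file 1, Appendix 2, which is not shown and may add contacts. Secondary endpoints are to be interpreted descriptively. Safety visits tied to an infusion are ordinary practice.

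The one-week visit may also be the second infusion, since the first course is two infusions seven days apart. That argues against making a common-visits-only analysis the main one, because reactions recorded at that visit could be lost from it.

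**What remains.** None of this removes the arm-B-only query and blood counts, or reverses their direction.

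**Conclusion.** The point holds as a modest inequality of ascertainment after month 4, to arm B's disadvantage, in mild, short-lived adverse events (endpoint 9) and transient laboratory abnormalities (endpoint 14). Expect about one arm-B-only visit per child, given the recovery figures and re-treatment assumptions above, and at most two. For evenly spread events the adverse-event excess is about 3% to 5% at the expected number of visits with 8 to 4 weeks' recall. It reaches about 37% only with roughly one week's recall and both visits held, and vanishes with four months' recall. Early clustering would make it larger by an unknown amount.

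Serious events would surface through unscheduled contact, infusion reactions are true treatment effects, and the primary log-rank test is unaffected. The matter is worth correcting because comparative safety is a stated aim and the correction is cheap. It does not invalidate the safety comparison.

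**What to change.** 1. Keep the planned all-sources comparison of adverse-event frequencies and rates as the main one.
2. Specify in the SAP, which the article says will be finalised before database closure, a sensitivity table of adverse-event rates after month 4 and of endpoint 14. It leaves out mild events and laboratory values first detected only at the 8-month-plus-one-week and 16-month-plus-one-week visits. Infusion reactions stay in, and no event leaves arm B's own safety table. The separate Table 3 columns should make these records identifiable.
3. Add a dated adverse-event line to the existing diary in both arms, transcribed at each visit. Report diary-sourced events separately: 70 of the 100 children were enrolled by 15 September 2020, so capture starts only when the line is introduced.
4. Reconcile the abstract's MMF start with the arm A description and Table 2.

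The cost is one extra table and a little data entry. No visit or treatment rule has to change for items 1 to 3.
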